**Fig 4 pone.0262216.g004:**
[figure not shown]
Emotional Go / No go sequence scheme. ISI: random time interval (2 to 6 seconds).

#### 4. Resting state sequence

We will ask subjects to keep their eyes closed, without falling asleep, and to stay unmoving for 10 minutes.

#### 5. Positive emotional periodic oscillatory stimulation sequence

See subpart 1 above: Negative & positive emotional periodic oscillatory stimulation sequence, and Fig 2.

### Post-MRI examination

After giving the participant a 15-minute break, the investigating psychiatrist will interview her. She will be asked to rate subjectively the emotional valence and intensity of each one of the 18 pictures of the emotional pictures viewing sequence, using the SAM scale created by the IAPS designers. This rating is from 1 to 9 for valence and intensity and assesses the cognitive part of the emotional experience of the subject.

Finally, we will ask the subject for her general experience of the protocol and the psychiatrist will give her contact information in case she needs to talk again about it. We will not include these data in the analyses.

### MRI data analysis

Functional (expect to periodic oscillatory stimulations) and structural scans will be pre-processed and analysed using SPM software (Statistical Parametric Mapping, Version 12, Revision 7219, Wellcome Department of Cognitive Neurology, London, UK). Images will be automatically realigned to each other, and we will apply a correction for head-motion using a 6-parameters rigid body spatial transformation. Finally, we will normalize all images to the Montreal Neurological Institute (MNI) space, and smooth them using a Gaussian kernel ([6
6
6] FWHM) in order to improve signal to noise ratio. We will also use TAPAS PhysIO Toolbox [38] to denoise functional volumes. We will model the GE-EPI time-series using a first level general linear model [39] with regressors representing expected BOLD fMRI response to visual stimuli of task (colour arrangement or picture), separately for each session. Realignment parameters are due to be added in the regression models to remove specific activation due to head movement (translations “right”, “forward”, “up” and rotations “pitch”, “roll”, “yaw”) and we will use a 128 second high-pass filter to remove non-physiological slow signal shifts.

We will calculate contrasted parameter estimate images (con-images) for each subject. Such images describe brain activation for every visual stimulus (emotional and go / no go paradigms). We will use CONN toolbox (www.nitrc.org/projects/conn, RRID:SCR_009550) for resting state analysis [40]. This analysis is based on the identification of standard physiological functional neuronal networks (“default mode” network, motor network, sensory network, visual network, attention network). We will carry out this identification out without any preconception, by an analysis of independent components (MATLAB version 2017a and toolboxes). We will assess connectivity forces with a Pearson correlation coefficient between each region concerned by the identified and compared networks, using a graph of this connectivity.

The fMRI signal from periodic oscillatory stimulations will be compared using BrainVoyager QX (Version 2.8.0, Brain Innovation, Maastricht, Netherlands). Pre-processing will consist in a linear trend removal to exclude scanner-related signal, a temporal high-pass filtering applied to remove temporal frequencies lower than three cycles per run, and a correction for small interscan head movements by a rigid body algorithm rotating and translating each functional volume in 3D space. We will spatially align functional (unsmoothed) data with the high-resolution anatomical volume which will be previously aligned to the AC-PC plane (automatic co-registration in BrainVoyagerQX, adjusted manually). Subsequently, the pre-processed functional data will be exported and analysed using custom scripts written in MatLab. Following the same procedure as in [41], we will perform a Fast Fourier Transform (FFT) on the pre-processed BOLD time series to get the amplitude spectrum. Then, we will calculate the mean and standard deviations of the amplitude of the 40 frequency bins neighbouring the stimulation frequency (20 on each side, e.g. in [42, 43]). Lastly as in previous studies [44], we will calculate the signal-to-noise ratio (SNR) of the response at the stimulation frequency by converting its amplitude to a z-score using the computed amplitude mean and standard deviations from the neighbouring frequencies. This procedure will be applied to each voxel independently. With this procedure, we should obtain the magnitude of neural response at the stimulation frequency (0.111 Hz) in the negative and positive emotional periodic oscillatory stimulation sequences.

As in [41], we will define the activation and deactivation of the neural response using the phase of BOLD response at the stimulation frequency. In general, a positive phase value indicates increasing BOLD response amplitude after the onset of the target stimuli, whereas a negative phase value indicates decreasing BOLD response amplitude after the onset of the target stimuli. To account for individual time differences to reach maximum BOLD response amplitude, we will plot a histogram (20 bins) of phase values of all the voxels with a z-score above 3 and with only a positive phase value, for each individual. We will use the phase value of the histogram bin that has the largest count as the centre phase (φ) and define all the voxels with their phase values within φ ± π/2 as activations (+ sign) and voxels with their phase values outside of this window as deactivations (- sign). We will then apply the signs to the thresholded SNR (z-score) maps to obtain a final response map containing only voxels that have increased BOLD response (+ sign) to the presence of the target stimuli. We will use a conservative statistical threshold (uncorrected, p < 0.001) to define areas selective to positive/negative emotional images corresponding to z-values above *3*.*09*).

We will finally import the resulting functional activation maps back to BrainVoyagerQX for visualization.

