### MRI data acquisition

We will instruct each subject to look closely at the pictures throughout their displaying during the MRI, but we will not warn the subjects that she will have to assess emotional valence and intensity of some of the shown pictures after the examination. This, in order to avoid bias introduced by control of their emotional experience [34] or the verbal quotation [35].

We will project task stimuli onto a translucent screen by a projector placed directly outside the magnet bore. Participants will see the screen via a mirror located in the head coil. Vision correction will be performed using non-magnetic glasses, which can vary in the range of -5 to +5 with 0.5 dioptre steps. We will forward-project all stimuli onto a screen in the MRI scanner room using ePrime software (Version 3.0, Psychology Software Tools Inc., Pittsburgh, PA, US) for emotional and Go/No Go paradigm and using a homemade software for oscillatory stimulation paradigms and a calibrated projector (Panasonic PT-AE500E).

We will acquire whole brain functional MR images using a 3-Tesla magnet (Magnetom Prisma; Siemens Healthcare GmbH, Germany) with a 64-channel receive-only head coil. For all participants, high-resolution anatomical images will be acquired using a 3D Turbo Flash sequence with the following parameters: TR = 2200ms; TE = 2.93ms; TI = 900ms; flip angle 8°; in plane resolution 0.89x0.89mm2; slice thickness 1mm. We will acquire 160 volumes parallel to the anterior–posterior commissural line, covering the whole brain extending from vertex to the inferior parts of the cerebellum.

We will get BOLD gradient echo–echoplanar images (GE-EPI) during all 5 functional MRI paradigms with the following imaging parameters: TE = 30ms, 40 axial slices, slice thickness 3mm, slices order: interleaved, in plane resolution 2x2mm^2^, no interslice gap, flip angle 77°. For these functional MRI sequences, TR will be adjusted on the paradigm’s design: TR = 2500ms for emotional, Go/No Go and Resting state one; and TR = 1500ms for periodic oscillatory stimulations. Total duration of MRI acquisition will be less than one hour.

Any adverse event occurring before or during the MRI examination will be reported on a dedicated support with the date and time. If needed, examination will be terminated at any time on participant’s request or on medical decision.

Five functional imaging sequences will be conducted and are described hereinbelow:

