#### 1. Negative emotional periodic oscillatory stimulation sequence

Sequences 1 & 5 are symmetrical in structure and both are described here. They differ in content and will be processed separately during the functional MRI imaging.

We selected pictures from the IAPS, NAPS and Geneva Affective Picture Database (GAPED) [36] databases according to their emotional valence and intensity in order to make 2 sub-groups of pictures: one with positive valence and high intensity emotional pictures (respectively rated > 6 and > 5.5), and one with negative valence and high intensity emotional pictures (respectively rated < 4 and > 5.5). We excluded sex-themed pictures of negative valence. We selected as simple as possible pictures in order to let the subjects quickly identify them as positive, neutral or negative.

Two series of 6 minutes 33 seconds each will be shown: in the first sub-sequence (Fig 2), negative images will be displayed at a frequency of 6 Hertz (6 pictures per second). Every 9 seconds, the software will insert a series of 7 positive pictures at a frequency of 3 Hertz (3 frames per second), alternating with negative pictures. In the second sub-sequence (Fig 2), positive images will be displayed at a frequency of 6 Hertz. Every 9 seconds, a sequence of 7 images with negative valence we will inserted, at a frequency of 3 Hertz, alternating with the positive images.

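### The oscillatory analysis signs voxels by BOLD phase from interleaved slices, with no listed slice-timing step and no statement that the phase window is circular

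*Protocol article*

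**What the plan says.** All references are to the Protocol article.

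- **Stimulus** (section 1, Negative emotional periodic oscillatory stimulation sequence): "Every 9 seconds, the software will insert a series of 7 positive pictures at a frequency of 3 Hertz". The opposite series has the same structure.
- **Acquisition** (MRI data acquisition): "40 axial slices, slice thickness 3mm, slices order: interleaved", with "TR = 1500ms for periodic oscillatory stimulations".
- **Pre-processing of these runs** (MRI data analysis): "Pre-processing will consist in a linear trend removal to exclude scanner-related signal", then a temporal high-pass filter and a rigid-body motion correction. Slice-timing correction is not named.
- **Sign rule** (MRI data analysis): for each participant, φ is the fullest of 20 histogram bins, counted over voxels with z above 3 and a positive phase. The plan will then "define all the voxels with their phase values within φ ± π/2 as activations (+ sign) and voxels with their phase values outside of this window"; the latter count as deactivations. Only + voxels stay in the final response map.
- **Gloss on the phase** (same section): a positive phase is said in general to mean an increasing response, "whereas a negative phase value indicates decreasing BOLD response amplitude after the onset of the target stimuli".

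The rule is attributed to a cited earlier study, which is not among the documents.

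**The concern.** The sign of a voxel, and so its place in the final map, is decided by phase alone. On a 9 s cycle one second is worth 40 degrees, so small timing errors matter. Three features of the written rule need attention.

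1. Slices in one volume are acquired at different times. If volumes are treated as instantaneous, a response in a late slice appears earlier than the same response in an early slice. This error is known and can be removed, but no listed step removes it.
2. Phase is an angle. Whether φ ± π/2 wraps at ±π is not stated, and the result depends heavily on it.
3. The gloss on negative phase and the window give different answers for the same voxel unless φ is exactly π/2.

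At stake is whether the + maps for the oscillatory runs show where the brain responded to the target pictures, or partly reflect slice position and a coding choice.

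**Working it through.** **Phase scale.** 1/9 s = 0.111 Hz, which reproduces the plan's stimulation frequency. One second = 360/9 = 40 degrees. The half-window of π/2 is 90 degrees, or 90/40 = 2.25 s.

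**Slice offset.** With 40 slices spread evenly over the TR, the last starts 39/40 × 1.5 = 1.4625 s after the first.
- Phase difference: 360 × 1.4625/9 = 58.5 degrees, and 58.5/90 = 65% of the half-window.
- Neighbouring slices in an interleaved order differ by about 0.75 s, or 30 degrees.
- If slices were taken two or four at a time (not stated), the maximum would be 57 or 54 degrees.
- If the 20 bins divide 0 to π, each is 9 degrees wide, so the spread covers about 58.5/9 = 6.5 bins of the histogram that locates φ.

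**Slice timing alone.** Since 58.5 is below 90, it cannot push a voxel out of a circular window. In the worst case a further 90 − 58.5 = 31.5 degrees, or 31.5/40 = 0.79 s, of true latency difference is needed.

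**Gloss against window.**
- φ = 60 degrees: the window is −30 to 150, so phases from −30 to 0 are signed + although the gloss calls them decreasing.
- φ = 120 degrees: the window is 30 to 210. Phases from 180 to 210 are recorded as −180 to −150. Read circularly they are signed +, against the gloss; read linearly they are signed −.
- φ = 90 degrees is the only value at which gloss and window agree.

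**Where φ is likely to lie.** This is an assumption. A double-gamma response to a burst of 7/3 = 2.33 s peaks at about 6.4 s at the fundamental frequency. With time zero at target onset and the usual Fourier sign, the phase is 360 − 40 × 6.4 = 104 degrees. That exceeds 90, so the window passes π in an ordinary case.

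**Size.** Simulation with assumed inputs: 30% of voxels truly deactivated, latency SD 1 s across voxels, phase noise 10 degrees, slice offsets uniform over 40 slices, 20 bins on 0 to π. Entries are the share of truly activated voxels signed as deactivations.

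| Mean peak | Circular, slices uncorrected | Circular, slices corrected | Linear on −π to π, slices uncorrected |
|---|---|---|---|
| 6.4 s | 4.5% | 3% | 17% |
| 6.0 s | 4.5% | 3% | 27% |
| 5.5 s | 4.5% | 3% | 43% |
| 5.0 s | 5.4% | 3% | 59% |
| 4.5 s | 11% | 3% | not needed here |
| 4.0 s | 21% | 6% | not needed here |

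The 3% follows directly. Latency SD 40 degrees and noise 10 degrees combine to √(40² + 10²) = 41.2 degrees; 90/41.2 = 2.18, and the two-sided normal tail is 2.9%.

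With latency SD 0.5 s and a circular window, uncorrected slices cost at most 0.3% for peaks of 5 to 7 s. The linear loss at 6.4 s is then about 5%. At SD 0.5 s and a peak of 4.25 s or earlier, the uncorrected rule can place φ on the deactivated voxels and reverse nearly all signs; with slice correction the error is about 0%.

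**Second calculation**, without phase noise or deactivated voxels, SD 1 s, base phase 104 degrees: circular loss is 3.9% with slice offsets and 2.5% without; linear loss is 15.7% and 4.0%. At a base phase of 150 degrees, linear loss is 51.0% with offsets and 23.7% without. Slice correction alone would therefore not rescue a linear comparison.

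**The case against.** The strongest reply is that a half-cycle window on an angle is naturally read as circular, and nothing in the article says otherwise. This stands. A reader might infer from the linear column that activated voxels are lost in bulk, but that needs a wrap-around fault in custom scripts that nobody has seen.

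A reader might also take the positive-phase limit to apply to the window. It applies only to the voxels that enter the histogram. The window is applied to all voxels, so a negative-phase voxel within π/2 of φ is signed + under a circular reading.

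A third inference is that latency differences between groups would pass for differences in activation. The article does not support this as it stands. φ is set for each individual, so the window moves with that person's latency. Under the circular reading the loss is nearly flat for peaks of 5 to 7 s, and acquisition is the same in all three groups. The Statistical analysis section does not say that the +-only maps feed the three-group comparison.

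The direction of the error (early-peaking or late-acquired voxels) also rests on a sign convention and time origin that the article does not give; the opposite convention reverses it.

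Finally, the cited study or the full protocol may settle slice timing and wrapping, and the gloss is introduced as a general remark. That lowers the weight of the point without removing it. The article gives its pre-processing as what the procedure consists of, and writes out the sign rule step by step. On those terms a known phase error of up to 58.5 degrees stays uncorrected and the gloss disagrees with the window.

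**Conclusion.** The point holds as an inexpensive improvement and a wording conflict to resolve. It is not a demonstrated error in the results.

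What follows from the article's own figures, given even slice spacing, is a slice-related phase spread of up to 58.5 degrees, no listed step to remove it, an unstated wrapping rule, and a gloss that matches the window only at φ = π/2.

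The size of the harm rests on assumptions about latency, its spread, the share of deactivated voxels and the phase convention. Under a circular window with latency SD 1 s, slice correction lowers mis-signing from about 4.5 to 5.4% to about 3% for mean peaks of 5 to 7 s, and from 11% to 3% at 4.5 s. With SD 0.5 s the gain over 5 to 7 s is negligible. The loss of about 17% at a 6.4 s peak, and more for earlier peaks, applies only if phases are compared linearly.

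**What to change.** In MRI data analysis, for the oscillatory runs:

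1. Correct each voxel's phase for its slice acquisition delay, by 360 degrees × delay/9 s (subtracted under the sign convention used above), or add slice-time correction to the listed pre-processing. If either is already done, say so.
2. Define activation as an absolute wrapped difference between the voxel's phase and φ of at most π/2. State the phase convention and the time origin.
3. Reword or remove the remark that negative phase means a decreasing response, so that it agrees with the window.

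Replacing the positive-phase histogram with another way of choosing the mode is optional; after items 1 and 2 it matters only for very early peaks (about 6% mis-signed at 4.0 s).

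The cost is a few lines in the MatLab scripts and a wording change, with no new data. Slice-time correction in pre-processing adds one interpolation step; correcting the phase directly avoids it.

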### Statistical analysis

Statistical analysis will include a descriptive analysis of all participants and a dedicated treatment for fMRI images, as presented hereinabove.

We will describe quantitative variables by their means and standard deviations, quartiles as well as the maximum and minimum values and qualitative variables by the respective percentages of each element. The rating scales’ scores will be calculated according to their authors’ recommendations.

Functional MRI data will be initially processed at individual level, and then at group level. We will create a map of significant differences, with risk corrected at whole brain level, and with a p-value lower than 0.05. We will make separate individual statistical analysis, with a t-test comparing brain activity between emotional tasks and rest sequence, then a group analysis for each study group, and finally a statistical comparison between the three groups. Amongst other inter-group and potentially intra-group sub-comparisons, we will conduct a dedicated sub-analysis to investigate potential differences between PNES with and without PTSD.

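### In the oscillatory analysis, z > 3.09 does not correspond to p < 0.001: the null rate is about 0.002 to 0.007 depending on the noise, so the uncorrected voxel threshold is not conservative

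*Protocol article*

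**What the plan says.** Under MRI data analysis, the two periodic oscillatory sequences have their own pipeline. The statistic is built in three steps. Each voxel's time series is Fourier transformed to give an amplitude at every frequency. For the noise reference, "we will calculate the mean and standard deviations of the amplitude of the 40 frequency bins neighbouring the stimulation frequency", half of them below it and half above. The response at 0.111 Hz is finally turned into a signal-to-noise measure "by converting its amplitude to a z-score using the computed amplitude mean and standard deviations from the neighbouring frequencies". All of this is done voxel by voxel, on unsmoothed functional data.

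The threshold follows: "We will use a conservative statistical threshold (uncorrected, p < 0.001) to define areas selective to positive/negative emotional images corresponding to z-values above" 3.09. Voxels are then signed by phase. Those within a half-circle around the participant's centre phase count as activations, and the final response map keeps only these + sign voxels.

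Under Statistical analysis there is a general rule for the fMRI data: "We will create a map of significant differences, with risk corrected at whole brain level, and with a p-value lower than 0.05". That section does not say whether the rule reaches the oscillatory maps.

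**The concern.** The article fixes the statistic, the cut-off and the p-value, and the three do not agree. The pair 3.09 and 0.001 holds for a standard normal variate with known mean and SD, tested one-sided. The quantity tested is the modulus of a Fourier coefficient. It cannot be negative, it has a long right tail under noise, and its centre and scale are estimated from 40 values. Both features push the exceedance rate above the normal value.

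At stake is what a reader may conclude from an area labelled selective in an individual map. Two of the four emotional sequences use this pipeline, and the Introduction hopes the work may eventually suggest targets for neuromodulation. A threshold described as conservative invites more trust in those areas than its real error rate supports. Noise voxels also enter one step earlier, because voxels with z above 3 and positive phase set each participant's centre phase.

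**Working it through.** **Inputs from the article.** Cut-off 3.09 and p < 0.001, uncorrected; 40 neighbouring bins; series of 6 min 33 s = 393 s; TR 1.5 s, hence 393 / 1.5 = 262 volumes; stimulation frequency 0.111 Hz; linear trend removal; + sign selection over half of the phase circle.

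**Assumption not in the article.** Gaussian noise, white as the base case and AR(1) with coefficient 0.3, 0.5 and 0.7 as the range.

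**Step 1, the article's own figure.** 1 − Φ(3.09) = 0.0010 one-sided (0.0020 two-sided). The stated pair is the one-sided normal conversion.

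**Step 2, estimating mean and SD from 40 bins.** Even for a normal variate the reference becomes t with 39 df in prediction form: P(t > 3.09 / √(1 + 1/40)) = 0.0020. The rate doubles before any skew is considered.

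**Step 3, the amplitude's own distribution, parameters known.** For a unit-scale Rayleigh variate the mean is √(π/2) = 1.2533 and the SD is √(2 − π/2) = 0.6551. The cut-off is 1.2533 + 3.09 × 0.6551 = 3.278, and P = exp(−3.278² / 2) = 0.0046.

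**Step 4, both features together.** Averaging exp(−c² / 2), with c = mean + 3.09 SD from 40 Rayleigh draws, over 2,000,000 sets gives 0.0071 (0.0077 if the SD uses divisor n).

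**Step 5, full Fourier simulation.** Detrended series, with either 262 volumes and target bin 44, or 258 volumes and target bin 43. Two run lengths were used because 393 / 9 = 43.67 cycles, so 0.111 Hz is not on a bin of the full run. The two agree closely.

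| Noise | P(z > 3.09) | P(z > 3.09 and + sign) | z cut-off for a true 0.001 |
|---|---|---|---|
| White | 0.007 | 0.0035–0.0036 | 4.1 |
| AR(1) 0.3 | 0.006 | 0.003 | 4.0 |
| AR(1) 0.5 | 0.004 | 0.002 | 3.8 |
| AR(1) 0.7 | 0.002 | 0.001 | 3.5 |

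**Step 6, what this means in voxels.** The article gives no voxel count. For an assumed 50,000 brain voxels, the nominal rate implies 50 null voxels above the cut-off. White noise implies 50,000 × 0.007 = 350, and AR(1) 0.7 implies 50,000 × 0.002 = 100. In the + sign map about half of these remain, roughly 175 and 50.

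**Step 7, an alternative statistic.** The ratio of power at the target to the mean power of the 40 neighbours follows F(2,80) when the spectrum is locally flat. Its 0.999 quantile is 7.54. In the same simulation, P(ratio > 7.54) is about 0.001 with white noise, 0.0006 at AR(1) 0.5 and 0.0004 at AR(1) 0.7.

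**The case against.** **Size.** The figure of 0.007 belongs to a flat noise spectrum and to the z rule before sign selection. The article gives no noise model, and its final map keeps only + sign voxels. This stands. The rate has to be given as a range, and in the final map at AR(1) 0.7 it falls to about the stated 0.001. Even there the threshold only meets its label and is not conservative.

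**Consistency with the corrected map.** A reader might infer that the uncorrected threshold and the whole-brain-corrected 0.05 rule contradict each other. The text does not support that. The oscillatory threshold is described for individual response maps that are then imported for visualisation, whereas the corrected rule concerns a map of differences, in a section that moves from individual to group level. The two can coexist. What remains is that the article does not say which rule governs the oscillatory maps.

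**Primary outcome.** A reader might also infer that the three-group comparison is compromised. Nothing makes this per-voxel cut-off the between-group test, the same cut-off applies to all 75 participants, and the z can serve as a response measure whatever threshold is displayed.

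**Status.** The study is exploratory and a pilot, the threshold is openly labelled uncorrected, and the procedure follows cited work that is not at hand. That lowers the severity but does not make the stated p-value correct.

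**Conclusion.** The point holds in moderate form. The conversion of z > 3.09 to p < 0.001 is wrong for this statistic. Its null rate is about 0.007 for a flat spectrum and about 0.006, 0.004 and 0.002 for AR(1) noise of 0.3, 0.5 and 0.7, which is 2 to 7 times the stated value. In the final + sign map the rate is about 0.001 to 0.0036. These figures assume Gaussian noise and whole-bin targets, and the choice within the range depends on a noise spectrum that the article does not give. In no case tried is the threshold conservative, and it is applied voxel by voxel without correction. The consequence shown is limited to the individual maps and to the areas called selective on them.

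**What to change.** - Replace the normal conversion. Either test the ratio of power at 0.111 Hz to the mean power of the 40 neighbouring bins against F(2,80), with 7.54 for p = 0.001, or keep the amplitude z and calibrate its cut-off to an empirical null.
- Do not hard-code one z value. The cut-off for a true 0.001 is about 4.1 with white noise and runs from about 3.5 to 4.1 across AR(1) 0.7 to 0. The F reference is exact for a locally flat spectrum and errs on the cautious side when the spectrum falls across the neighbouring bins.
- Delete the word conservative.
- Add one sentence saying whether the whole-brain correction under Statistical analysis covers the oscillatory maps or only the group-difference maps.

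Cost: a few lines in the custom MatLab script and a short wording change, with no new data and no burden on participants. The individual maps will show fewer voxels.
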